## Abstract

**Background:**

Diabetes is the western world’s leading cause of end-stage renal disease. Glucose-dependent, oxidative stress is linked to the development of renal inflammation and sclerosis, which, in animal models of diabetes, can be prevented by anti-oxidative treatment. Patients of non-Caucasian heritage have low activity of the selenoprotein, antioxidant enzyme, glutathione peroxidase (GPx) and its co-factor vitamin E, which may be linked to their increased propensity to developing end-stage renal disease.

**Research design and methods:**

We have designed a double-blind, randomized, placebo controlled study with selenium and/or vitamin E versus placebo as the interventions for patients with type 2 diabetes and chronic kidney disease (CKD) stages 1–3. A 2 × 2 factorial design will allow a balanced representation of the heritage groups exposed to each intervention. The primary biochemical outcome is change in GPx activity, and clinical outcome measure is the actual, rate of—and/or percentage change in estimated glomerular filtration rate (eGFR) from baseline. Analysis will be with a marginal model for longitudinal data using Generalized Estimating Equations corrected for measures of baseline serum antioxidant enzyme activities (GPx, superoxide dismutase and catalase), micronutrient levels (vitamins E and C), measures of inflammation (interleukin 6, c-reactive protein and monocyte chemoattractant protein-1) and markers of oxidative damage (plasma 8-isoprostaglandin F2α and urinary 8-hydroxydeoxyguanosine).

**Expected results:**

The study will assess the relationship between GPx activity, oxidative stress, inflammation and eGFR. It will test the null hypothesis that antioxidant therapy does not influence the activity of GPx or other antioxidant enzymes and/or alter the rate of change in eGFR in these patient groups.

**Conclusions:**

Outcome data on the effect of antioxidants in human diabetic renal disease is limited. Previous post hoc analyses have not shown a beneficial effect of vitamin E on renal function. A recent trial of a pharmaceutical antioxidant agent, improved eGFR, but in patients with advanced diabetes-related chronic kidney disease its use was associated with an increased incidence of cardiovascular events. We will explore whether the nutritional antioxidants, vitamin E and selenium alone, or in combination in patients at high risk of renal disease progression, forestalls a reduction in eGFR. The study will describe whether endogenous antioxidant enzyme defenses can be safely modified by this intervention and how this is associated with changes in markers of oxidative stress.

*Trial registration* ISRCTN 97358113. Registered 21st September 2009

## Background

Diabetes is the leading cause of end-stage renal disease (ESRD) which has a predilection for persons of non-white heritage [1]. Comparative international, and national studies suggest that the rate of progression of chronic kidney disease (CKD) is higher in patients of non-white heritage than those of Caucasian heritage [1–3]. In a post hoc analysis of the United Kingdom Prospective Study, an independent relationship was found between non-white ethnic heritage, albuminuria and renal impairment [4]. These observational data suggest that heritable and/or shared environmental factors play a role in the susceptibility to, and progression of renal disease in patients with diabetes.

Hyperglycaemia increases the production of reactive oxygen species (ROS) which are capable of damaging lipid and DNA molecules. Oxidative stress occurs when ROS production overwhelms the host’s capacity to remove them which then causes upregulation in transcription factors such as NF-κB and elaboration of pro-inflammatory cytokines and chemokines. These biochemical events limit the availability of the vasodilator nitric oxide, which interferes with the regulation of blood flow and vasoprotective functions of the endothelium [5]. In experimental studies, these changes have been shown to be determinants of the development of diabetic kidney lesions which can be ameliorated with antioxidant treatment. In a rodent model of type 2 diabetes and kidney disease, vitamin E given as an antioxidant therapy, restored antioxidant enzyme activity and reduced oxidative damage of renal tissue [6]. This has led to suggestions that strategies to enhance endogenous antioxidant mechanisms could help prevent microvascular diabetic complications [7].

Markers of oxidative stress are increased in the circulation and renal tissue of patients with diabetes compared with control patients without diabetes [8, 9]. Patients of African origin have been found to have higher circulating levels of lipid peroxide, lower concentrations of vitamin E and faster rates of decline in renal function compared with those of Caucasian heritage [10, 11]. Relatively low levels of serum selenium have been reported in people of Asian origin [12]. Selenium is a co-factor for the antioxidant enzyme GPx, and low levels are associated with an upregulation of inflammatory chemokines. Selenium supplementation attenuates the inflammatory response and in systemic inflammatory disease states may improve clinical outcomes [13, 14].

The activity of GPx in plasma is largely derived from renal tubular epithelium and is reduced in the presence of renal disease [15, 16]. It is unclear whether the level of activity of GPx contributes to the susceptibility to progressive renal disease. In this study, we will compare the effect over time of antioxidant therapy with vitamin E and/or selenium in patients with type 2 diabetes and early CKD, on measures of systemic inflammation, antioxidant enzyme activity and changes in eGFR.

## Subjects

We plan to recruit a total of 200 adult patients with type 2 diabetes of white, Caucasian and non-Caucasian (African, Caribbean or Indo-Asian) heritage from general practices in South West London, UK. An equal number of eligible patients will be randomized to receive, either, active selenium (200 μg once daily) or its placebo and/or vitamin E (400 IU once daily) or its placebo in a 2 × 2 factorial design (Fig. 1). Treatment allocation will be according to a computer generated code for each group to which the patients and researchers will be blinded.

**Fig. 1 Fig1:**
[figure not shown]
Flow diagram of the recruitment, randomization and follow-up of eligible patients double-blind, randomized placebo controlled trial into the 2 × 2 factorial, to achieve balanced representation of non-Caucasian and Caucasian heritage groups

Type 2 diabetes mellitus will be diagnosed according to WHO criteria. Eligible patients will have hypertension (3 consecutive sitting blood pressure readings >140 systolic and/or diastolic 90 mmHg without treatment or receiving treatment for known hypertension) and early CKD defined as an eGFR > 45 and <90 mL/min/1.73 m^2^ and/or urinary albumin:creatinine ratio >3 mg/mmol.

Patients will be excluded if they have any of the following: a history of cardiovascular disease, defined as having a clinical record of ischaemic heart disease (angina, myocardial infarction, coronary artery revascularization and or heart failure), peripheral vascular disease (intermittent claudication or peripheral artery revascularization) or cerebrovascular disease (transient ischaemic episodes or stroke), a history of malignancy or any other life threatening illness, current pregnancy, systolic blood pressure >200 mmHg, diastolic blood pressure >160 mmHg, haemoglobin A1c > 86 mmol/mol (10 %), significant renal impairment (eGFR < 45 mL/min 1.73 m^2^) and nephrotic range urine protein excretion (total protein excretion rate >3 g/day or albumin:creatinine ratio >300 mg/mmol).

The medical, family, social and treatment histories, and the clinical and biochemical measurements collected at the in-person visits will be recorded using a standardized, electronic proforma. Dietary intake and patterns will be evaluated using a 3-day food diary to assess components of the usual diet (Dietplan 6, Forestfield Software Ltd, Horsham, West Sussex, UK).

## Methods

Anthropometric measures will include height in metres, weight in kilogrammes, and waist circumference in centimetres. Body mass index will be calculated from the weight in kilogrammes divided by the height in metres squared. Sitting blood pressure will be measured by digital oscillometry (Omron 705IT, OMRON Healthcare Europe, The Netherlands) according to the National Institutes of Health and Care Excellence guidance (http://www.nice.org.uk/guidance/cg127).

Patients will undergo routine clinical assessments for the complications of diabetes. The presence or absence of retinopathy will be reviewed on an annual basis by standardized, digital retinal fundal photography which will be reported according to National Health Service guidelines by retinal screeners who are unaware of the patient’s participation in the study (http://www.diabeticeye.screening.nhs.uk/gradingcriteria). Peripheral neuropathy will be assessed according to responses to testing with a 10 g monofilament. Peripheral vascular disease will be assessed by the appreciation of the dorsalis pedis and posterior tibial artery pulsation by digital examination. Patients will also be screened for ischaemic heart disease in response to modified questions from the Rose questionnaire [17] and have 12-lead resting electrocardiography (Seca CardioConcept 5.6, Seca UK) performed and read using Novacode criteria [18].

### Arterial stiffness

Finger plethysmography is a non-invasive method to assess changes in finger blood flow that will be used as a proxy measure of arterial stiffness. The pulse wave amplitude will be measured from the finger-tip using infra-red light (PulseTrace PCA2, CareFusion UK 232 Ltd, Basingstoke). The contour of the finger pulse will then be automatically analysed to determine a stiffness index which has been shown to be correlate with pulse wave velocity after adjustment age, sex, height, and weight [19].

### Biochemical assessments

Venous blood will be sampled after a 12 h fast. Measurements will be performed to allow several domains of the study to be addressed, including lipids, systemic inflammation, oxidative damage and stress, diabetes control and nutrition. Deoxyribonucleic acid (DNA) will be extracted from whole blood using a salting-out method as described by Miller et al. [20] for the subsequent analysis of genetic polymorphisms of the antioxidant enzymes being investigated.

Plasma creatinine will be used to estimate renal function—using the modification of diet in renal disease (MDRD) and CKD-EPI equations. Three early morning urine samples will be collected for estimation of the median albumin: creatinine ratio. Aliquots of the urine, whole blood and blood separated into serum and plasma will be stored at −70 to −80 °C for later analysis of the key outcome variables described below.

Glutathione peroxidase activity will be measured as described previously by Zitouni et al. [11]. In brief, 500 μL Tris–HCl (0.2 mmol/L, pH 8) will be mixed with NADPH (0.2 mmol) followed by 100 μL EDTA (5 mmol/L) and 100 μL glutathione (20 mmol/L). Plasma (100 μL) will then be mixed with glutathione reductase (0.002 units) and incubated for 5 min at 37 °C and for a further 5 min after the addition of 100 μL of tert-butyl hydroperoxide (0.7 mmol/L). Absorbances will be read in a spectrophotometer at 340 nm. A unit of GPx activity is defined as being equivalent to the oxidation of 1 μmol of NADPH per second at 37 °C. The intra-assay coefficient of variation (c.v.) is 3.2 %.

Catalase activity in plasma will be measured using a fluorometric assay. Plasma (50 μL) will be mixed with 400 μL phosphate buffer (100 mmol, pH 7) followed by 50 μL horseradish peroxidase (40 U/ml) and 100 μL of hydrogen peroxide (3.3 μmol/L). The samples will then be vortex-mixed and incubated for 10 min at room temperature. After incubation, 50 μL of hydroxyphenyl acetate (50 mg/mL) will be added and the fluorescence of the product will be read in a fluorometer (excitation 320 nm and emission 400 nm). Within-run c.v.’s are 2 % for standards and samples, whereas the between-run c.v. are 3.1 % for standards and 7.3 % for samples.

Extracellular SOD activity will be measured in relation to the inhibition of the rate of nitro blue tetrazolium (NBT) reduction in the presence of xanthine and xanthine oxidase yielding a purple colour [11]. Plasma (500 μL) will be treated with 300 μL chloroform and 500 μL ethanol. The samples will then be centrifuged at 18,000 × *g* for 30 min, and 50 μL of the supernatant will be removed and mixed with 900 μL of SOD reagent [0.1 mmol/L xanthine, 0.1 mmol/L EDTA, 50 mg bovine serum albumin, 25 mmol/L NBT and 40 mmol/L Na_2_CO_3_ (pH 10.2)]. Twenty-five units of xanthine oxidase will then be added, and the samples will be incubated for 20 min at 25 °C. The reaction will be stopped by the addition of 1 mL CuCl_2_ (0.8 mmol/L), and the absorbance of the samples will be measured at 560 nm. The intra-assay c.v. is 3.5 %.

Vitamin E as plasma α- and γ-tocopherols will be measured using a high-performance liquid chromatography system with ultraviolet detection and tocopherol acetate as internal standard. Briefly, plasma (100 μL) will be combined with 3 μg α-tocopherol acetate and 500 μL hexane. The upper layer will be aspirated after centrifugation, and lipid extraction will be performed twice. The solvent will be evaporated to dryness under a stream of nitrogen. The residue will be dissolved into 400 μL methanol and 20 μL will be injected onto the high performance liquid chromatography system. α-Tocopherol and γ-tocopherol concentrations in the samples will be calculated by relating their peak areas to that of the internal standard. The plasma contents of absolute and lipid standardized vitamin E will be expressed relative to triglyceride, cholesterol, or triglyceride and cholesterol.

The total cholesterol content of plasma will be measured by an enzymatic colorimetric method (Cholesterol CHOD-PAP; Sigma Diagnostic). Briefly, an aliquot of plasma sample (10 µL) will be incubated with a reagent (900 µL) containing: detergent, cholesterol esterase, and cholesterol oxidase. Hydrogen peroxide produced as a result of cholesterol oxidase activity is used to oxidise aminoantipyrene to give a pink product, the absorption of which will be measured in a spectrophotometer at 500 nm.

The total triglyceride contents of plasma and lipoprotein fractions will be measured by an enzymatic colorimetric method (Triglycerides GPO-PAP; Sigma Diagnostics). In brief, an aliquot of plasma sample (10 µL) will be mixed with 900 µL of a reagent containing a lipase to deacylate triglycerides and liberate glycerol. This will then be phosphorylated to glucose-1-phosphate and the product oxidised by glucose phosphate oxidase with the formation of hydrogen peroxide (H_2_O_2_). The H_2_O_2_ formed will then be coupled with horseradish peroxidase to give a pink product, the absorption of which will be measured in a spectrophotometer at 500 nm.

Vitamin C as total ascorbate (sum of oxidised and reduced ascorbate) will be measured by enzymatic oxidation of reduced ascorbic acid to dehydroascorbate acid followed by reaction of the dehydroascorbate formed with o-phenylenediamine to give a fluorescent product [21]. Two hundred and fifty microliters of plasma will be mixed with 250 μL metaphosphoric acid (20 % w/v) and centrifuged at 13 000×*g* for 5 min. 50 μL of the supernatants will be combined with 900 μL of sodium acetate buffer (2 mol/L, pH 6.2) and ascorbate oxidase (10 μL of 1 U/1 μL in sodium acetate buffer). o-1, 2-diphenylenediamine (20 μL, 1 mg/mL) is then added and the samples are incubated for 30 min at room temperature in the dark. Finally, the fluorescent signals will be read in spectrofluorometer at excitation at emission wavelengths of 350 and 430 nm, respectively. The inter- and intra-assay c.v. are 1 and 2.5 %, respectively.

Selenium will be measured in serum as described by Rayman et al. [22]. The analysis will be carried out at the SAS Trace Element Unit, Southampton General Hospital using dynamic reaction cell-inductively coupled plasma MS on an Elan 6100 DRC plus (SCIEX Perkin-Elmer).

Oxidative stress will be assessed by measuring (1) plasma and urinary free 8-iso prostaglandin F2α using an ELISA kit (Cayman Chemical, Ann Arbor, MI, USA) and (2) urinary 8-hydroxydeoxyguanosine (8-OHdG) as a marker of deoxyribonucleic acid damage using an ELISA kit according to the manufacturer’s instructions (Cambridge Biosciences Ltd, Cambridge, UK).

Inflammation will be assessed by measuring c-reactive protein, interleukin-6 and monocyte chemoattractant protein-1 by ELISA kits according to the manufacturer’s instructions (ThermoFisher Scientific, Paisley, UK).

### Clinical follow-up procedures

All patients will receive their usual care according to the latest National Institutes of Clinical Excellence recommendations, in primary and secondary care settings [23]. Treatment will aim to achieve targets for blood pressure of ≤130/80 mmHg, glycated haemoglobin of 59 mmol/mol (<7.5 %) and LDL-cholesterol of ≤2 mmol/L (<100 mg/dL). Routine clinical and biochemical measurements and outcome assessments will be performed at the baseline visit and 1, 3, 6, 12, 18 and 24 months after randomization. All of the patient’s data will be anonymized.

### Statistical analysis

In this 2 × 2 factorial design, selenium and vitamin E are considered the two factors. The data will be analyzed with a linear mixed model for longitudinal data [24]. In the model, eGFR is the dependent variable and time is an independent variable; the model will also contain as independent variables a dummy variable for each of the two factors, a term for the two-way interaction between the two factors, and continuous covariates for various measures of oxidative stress and inflammation at baseline. The model allows for the correlation between repeated measures on the same individual, but assumes that there is independence from one subject to the next. The correlation within measurements on a given subject will be modeled using compound symmetry as well as an autoregressive correlation structure. Whichever structure gives the best fitting model to the data will be used.

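### The stated eGFR model has no treatment-by-time term, so it estimates an average level difference and cannot test the rate-of-change hypothesis or separate an early shift from slower decline

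*Protocol article*

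**What the plan says.** The Abstract (Expected results) states the null hypothesis on eGFR in terms of its rate of change, and the closing Conclusions section names decline in renal function as the main target. The Abstract (Research design and methods) defines the outcome more loosely: "clinical outcome measure is the actual, rate of—and/or percentage change in estimated glomerular filtration rate (eGFR) from baseline".

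The Statistical analysis section specifies a linear mixed model: "In the model, eGFR is the dependent variable and time is an independent variable". The treatment terms are "a dummy variable for each of the two factors, a term for the two-way interaction between the two factors", together with baseline measures of oxidative stress and inflammation. Within-subject correlation is to be "modeled using compound symmetry as well as an autoregressive correlation structure", with the better-fitting structure kept. No product of treatment and time appears.

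Outcome assessments are "performed at the baseline visit and 1, 3, 6, 12, 18 and 24 months after randomization". The Results section makes the selenium by vitamin E interaction the primary hypothesis, with main effects to follow if there is none. It bases effect sizes on change from baseline to one year. It speaks of comparing eGFR slopes only for heritage or oxidative-stress groups, not for treatment arms.

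**The concern.** In a repeated-measures model with a treatment dummy and a time term but no product of the two, the arms are forced to run parallel. The dummy then measures how far apart they are on average. That is not an effect on the rate of change, which is what the hypothesis names.

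The gap matters because two different effects feed the same coefficient: a shift in eGFR soon after starting treatment that leaves later decline unchanged, and a genuine slowing of decline. The article's own mechanism makes a shift possible. It says of oxidative stress: "These biochemical events limit the availability of the vasodilator nitric oxide, which interferes with the regulation of blood flow". An agent acting on that pathway could move eGFR through blood flow. If a shift occurred and were sustained on treatment, the planned coefficient could be taken as evidence of slower progression. An early fall followed by real slowing could look null. The primary interaction contrast has the same limitation, because it too is a contrast of levels.

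**Working it through.** **Plan's own figures.** For an interaction contrast in four equal cells, SE = 4 SD/√N.
- N = 150, effect 1.0 SD: 1.0/(4/√150) = 3.06; 3.06 − 1.96 = 1.10; power 86.5% (stated 85%).
- N = 200, effect 0.85 SD: 0.85/(4/√200) = 3.01; 3.01 − 1.96 = 1.05; power 85.2% (stated 83%).

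With t quantiles these are 86.0% and 84.9%. The stated figures fit the interaction test. They neither support nor weaken the present point.

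**Inputs.** Visits at 0, 1, 3, 6, 12, 18 and 24 months (Clinical follow-up procedures). Compound symmetry or autoregressive correlation (Statistical analysis). Assumed: complete data, and baseline eGFR as one of the repeated outcomes, since it is not among the listed covariates. D (a shift held from month 1) and b (true slowing per year) are symbols; the documents give no value for either.

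**Step 1: the model as listed.** Under compound symmetry with complete data, the treatment coefficient is the mean difference over the seven visits, whether time is coded as linear or by visit.
- Held shift: (0 + 6 x D)/7 = 0.857 x D. Under autoregressive structures with correlation 0.5 to 0.9 (assumed) it is 0.58 to 0.78 x D.
- True slowing: mean visit time = 64/7 = 9.143 months = 0.762 years, giving 0.762 x b.
- Equivalence: 0.857/0.762 = 1.125. A held shift of 1 mL/min/1.73 m² and a slowing of 1.125 per year give the same coefficient.

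If baseline is left out of the outcome vector, the multipliers become 1.00 x D and (64/6)/12 = 0.889 x b. The ratio is again 1.125.

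**Step 2: add treatment-by-time only, baseline in the line.**
- Sum of squares of time: 1090 − 64²/7 = 504.86 months².
- Cross-product with a unit step after baseline: 9.143.
- False slope: 9.143/504.86 = 0.01811 per month = 0.217 x D per year.

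For D = 1 to 3 (assumed) that is 0.22 to 0.65 mL/min/1.73 m² per year with no true slope effect. Forcing a common baseline, with a random intercept (SD 15) and random slope (assumed), gives 0.23 to 0.26 x D.

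**Step 3: add a post-baseline shift as well.** The step term absorbs a held D, and the slope bias is 0.

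**Step 4: a shift that wanes on treatment.** Take differences of 1, 1, 0.5, 0, 0, 0 at months 1 to 24.
- Listed model: 2.5/7 = +0.36.
- Slope through baseline: −15.857/504.86 x 12 = −0.38 per year.
- Shift-plus-slope model: the later slope rests on months 1 to 24, with sum of squares 1090 − 64²/6 = 407.33, giving −19.667/407.33 x 12 = −0.58 per year.

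Level and slope then point in opposite directions, and the step term does not cure it.

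**Step 5: precision.** With arm-specific intercepts, the ratio of standard errors (shift-plus-slope against single slope) is √[(s² + e²/2.829)/(s² + e²/3.506)]. Here s is the slope SD, e the residual SD, 2.829 = 407.33/144 and 3.506 = 504.86/144.
- e = 4, s = 2: √(9.66/8.56) = 1.06.
- e = 4, s = 3: √(14.66/13.56) = 1.04.
- e = 8, s = 2: √(26.62/22.25) = 1.09.
- e = 8, s = 3: √(31.62/27.25) = 1.08.
- Compound symmetry (s = 0): √(504.86/407.33) = 1.11.

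All of these SDs are assumed. With a common baseline, the pairs (4, 2) and (8, 3) give 1.07 and 1.09.

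**Step 6: the primary contrast.** With shifts D(Se), D(E) and D(both), the interaction coefficient picks up 0.857 x [D(both) − D(Se) − D(E)]. It is zero if the shifts add, and not otherwise. Additive shifts reappear in the main effects, which the plan estimates when no interaction is found.

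**The case against.** The strongest reply is that this is a condensed article. Coding of time, a split into early and late effects, and sensitivity analyses may sit in a full protocol or analysis plan that is not shown, and their absence alone would be no finding. That is right as far as it goes. But the article does list its model terms and does state a hypothesis about rate, and the two do not match. That is a point about what is stated.

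A second reply is that an early shift is speculative. This largely stands. A reader might infer that the article itself reports an early, reversible rise for another antioxidant, but it does not. It says "A recent trial of a pharmaceutical antioxidant agent, improved eGFR, but in patients with advanced diabetes-related chronic kidney disease" its use was associated with more cardiovascular events. Nothing is said about timing or reversibility. The vasodilator passage supports the possibility of a shift and no more.

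Third, the article names actual change in eGFR among its outcomes, and on that outcome a sustained difference is real, not false. This also stands. The error arises only if a level difference is read as a difference in rate.

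Fourth, additive shifts cancel in the primary interaction contrast. That is true, but it does not protect the main effects (step 6).

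**Conclusion.** The point holds in this form: the listed model does not estimate the quantity in the rate-of-change hypothesis, and its treatment coefficients mix an early shift with slower decline at 0.86 x D and 0.76 x b under compound symmetry. Adding treatment-by-time alone leaves 0.22 x D per year of false slope if a shift is held. These multipliers follow from the visit schedule, the stated correlation structure and complete data.

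Whether a shift will occur, and how large, is not in the documents. A reader might go further and conclude that an inert supplement would be reported as renoprotective, or put a false-positive probability on it. The documents do not support that. Any such probability depends on assumed values of D and the variances, and a waning shift would make a from-baseline slope look like faster decline. Nor can the slope comparison in the Results section be read as a comparison of treatment arms. The fault is a mismatch between hypothesis and model that can be put right before analysis, not a demonstrated bias of known size.

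**What to change.** In the eGFR model, add two terms for selenium, for vitamin E and for their interaction: treatment by time, and treatment by a post-baseline indicator. Let the common time course be by visit, or include the post-baseline indicator itself, so that the reference arm can also step. Report three estimates for each contrast: the early shift, the later slope per year, and the 24-month difference (shift + 2 x slope). State in advance that any claim about rate of decline rests on the slope term and not on a level difference alone. Add that the three estimates are read together, because a shift that wanes on treatment still distorts the later slope.

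The months 1 and 3 visits already scheduled ("at the baseline visit and 1, 3, 6, 12, 18 and 24 months after randomization") supply the data, so no new visits or samples are needed. The cost is a revised model statement, six extra coefficients and a larger standard error for the later slope. Against a single-slope model that increase is about 7% to 9% under the assumed common-baseline variances, and between 4% and 11% across the arm-specific-intercept cases in step 5.

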## Results

The primary hypothesis of interest in this study is whether there is an interaction between the selenium and Vitamin E supplements. If interaction is present, then the effect of each supplement will have to be estimated separately in the presence and absence of the other supplement. If no interaction is present, then it will be possible to estimate the main effects of selenium and Vitamin E separately without having to take the other supplement into consideration.

The effect sizes are conservative and will be based on the estimated changes from baseline to 1 year [25]. A study population of 150 will have 85 % power to detect an ES of 1.0 SD, and a population of 200 will have 83 % power to detect an ES of 0.85 SD at a two-sided alpha level of 5 % [26].

The two heritage groups will have their eGFR slopes compared over time and considered as either, (a) Caucasian and non-Caucasian, or (b) High and Low levels of oxidative stress/inflammation, with the oxidative stress and inflammation markers dichotomized at their median value. The power will not be heavily dependent on any of the assumptions; regardless of the true value of the underlying correlation among observations with subjects, of the correlation structure, of the attrition rate, or of the number of repeated measurements.

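### The listed eGFR model has no treatment-by-time term and no baseline eGFR, so its treatment coefficients estimate average level differences, not the rate of change or change from baseline that the trial asks about

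*Protocol article*

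**What the plan says.** The Statistical analysis section describes a linear mixed model in which "eGFR is the dependent variable and time is an independent variable". It adds that "the model will also contain as independent variables a dummy variable for each of the two factors, a term for the two-way interaction" between them, and the remaining terms are "continuous covariates for various measures of oxidative stress and inflammation at baseline". The section defines the two factors as selenium and vitamin E, so the only interaction named is the one between the supplements. Within-patient correlation is to be compound symmetry or autoregressive, whichever fits better.

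The questions that this model has to answer are stated elsewhere:

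- Abstract, Expected results: the null hypothesis is that therapy does not "alter the rate of change in eGFR in these patient groups".
- Abstract, Research design and methods: the clinical outcome is the actual change, the rate of change and/or "percentage change in estimated glomerular filtration rate (eGFR) from baseline".
- Results: the supplement interaction is the primary hypothesis, and effect sizes rest on the change over the first year. Slopes are mentioned for other groups only: "The two heritage groups will have their eGFR slopes compared over time".
- Clinical follow-up procedures: measurements are "performed at the baseline visit and 1, 3, 6, 12, 18 and 24 months after randomization".

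**The concern.** With time entered once and crossed with nothing, the model draws four parallel lines. A supplement can move its line up or down by a constant, but it cannot tilt it. The selenium and vitamin E coefficients, and the product term, are then differences in average eGFR over whichever visits are in the response. They are neither slope differences nor changes from baseline.

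Two consequences follow if the model is run as listed. First, a slowing of decline builds up with time, so averaging it over early visits shrinks it. Second, because neither the response nor the covariates take out each patient's starting eGFR, the comparison carries the full between-patient spread, and a chance difference between arms at baseline passes into the treatment coefficient.

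**Working it through.** **The plan's own power figures.** These fit the supplement interaction as a difference of differences between four cell means, with N/4 patients per cell and SE = SD x sqrt(4/(N/4)).

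- N = 150: SE = sqrt(4/37.5) = 0.327 SD, so 1.0 SD is 3.06 SE. Power is 86.0% by noncentral t, against 85% stated.
- N = 200: SE = sqrt(4/50) = 0.283 SD, so 0.85 SD is 3.01 SE. Power is 84.9%, against 83% stated.

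The figures are close, so they are not the problem. They refer to a change from baseline to one year, which the listed model does not estimate either.

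**Terms against questions.**

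| Question in the article | Term needed | Listed? |
|---|---|---|
| Supplement alters rate of change | time x supplement | No |
| Supplement interaction, on rate of change | time x selenium x vitamin E | No |
| Change from baseline | change as the response, or baseline eGFR taken into account | No |
| Heritage or marker-group slopes | time x group | No |

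**Inputs for the size.** From the article: visits at 0, 1, 3, 6, 12, 18 and 24 months; 200 patients in equal arms, so 100 per level of each factor. Assumed, because the article gives no variances: between-patient SD 13, visit-to-visit SD 5 and slope SD 3 (range 2 to 4) mL/min/1.73 m² per year; main-effect benefit 1.5 per year; complete data. Power = Phi(estimate/SE - 1.96) plus the opposite tail. A two-group SE is sqrt(4 x variance/200).

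Visit times: the mean is 64/7 = 9.14 months = 0.762 years, and the sum of squares about the mean is 3.506 years². Under compound symmetry with baseline in the response, a pure slope effect enters the treatment coefficient as 9.14/24 = 38% of the 24-month difference.

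1. *Listed model, baseline visit in the response.* Estimate 1.5 x 0.762 = 1.14. Variance of a patient mean = 13² + 3² x 0.762² + 5²/7 = 177.8; SE 1.89; power about 9%.
2. *Listed model, six post-baseline visits, unadjusted.* Mean time 64/6 months = 0.889 years; estimate 1.33. Variance = 169 + 9 x 0.889² + 25/6 = 180.3; SE 1.90; power about 11%.
3. *As 2, with baseline eGFR adjusted for (not listed).* Variance = 180.3 - 169²/(169 + 25) = 33.1; SE 0.81; power about 37% (42% to 33% for slope SD 2 to 4).
4. *Treatment x time.* Estimate 1.50. Variance = 3² + 25/3.506 = 16.13; SE 0.57; power 75% (89% to 60%).
5. *Supplement interaction in slopes, same size.* SE doubles to 1.14; power about 26% (36% to 20%).

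**Correlation structure.** If treatment x time is added but compound symmetry is kept while slopes truly vary, the model takes the slope variance as roughly [(6 x 25 + 9 x 3.506)/6]/3.506 = 8.63 instead of 16.13. A nominal 1.96 is then really 1.96 x sqrt(8.63/16.13) = 1.43, a two-sided error rate of about 15% (10% to 20% for slope SD 2 to 4).

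**The case against.** **The list may be condensed.** This is a journal article, and the Results section promises slope comparisons between heritage groups that the listed model could not deliver. Time interactions may therefore have been dropped in the telling, and nothing says that the list is exhaustive. This limits how sure one can be that the trial will be run this way. It does not clear the text: the section sets out the treatment terms one by one, names one interaction, and does not name the one that the null hypothesis needs.

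**Slope is not the only outcome.** The abstract offers three forms of change, and the effect sizes use the change to one year. A reader might infer that treatment can act only through the slope. The documents do not say so; the abstract's Conclusions mention another antioxidant that improved eGFR, so a level shift is possible. The listed model still serves that case poorly, because without baseline eGFR it does not measure change.

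**The model is not blind.** A reader might also infer that it cannot respond to a slope effect at all, or that a real benefit would almost certainly be missed. Neither follows. Part of a slope effect reaches the treatment coefficient: 38% of the 24-month difference under compound symmetry, and 41% to 47% under an autoregressive structure (correlation 0.5 to 0.9). For an assumed 24-month difference of 0.3 SD, the level term against the slope term has 13% to 19% against 80% to nearly 100% under compound symmetry, but 21% to 32% against 38% to 67% under the autoregressive structure. The 9% figure is the unadjusted worst case.

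**Conclusion.** The point holds as a mismatch between the stated model and the stated question. It can be read off the list of terms and needs no assumed number. The treatment coefficients, including the one for the primary interaction hypothesis, are average differences in eGFR level.

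The size of the loss does rest on assumed variances, a purely slope-based benefit and complete data. For a main effect, power runs from about 9% to 11% as listed, to about 37% had baseline eGFR been adjusted for, to 75% for the slope term. The ranking is the same in every case worked here, but the gap narrows with baseline adjustment and under autoregressive correlation. Correcting the model does not make the primary interaction test strong: a slope interaction of 1.5 per year would still have only about 26% power under the same assumptions.

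**What to change.** In the Statistical analysis section:

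- Add time x selenium, time x vitamin E and time x selenium x vitamin E as required terms.
- Give the arms a common baseline mean, or include baseline eGFR as a covariate.
- Use a random intercept and slope per patient in place of compound symmetry alone, so that the slope tests keep their error rate.
- Test the three-way term for the primary interaction hypothesis.
- Report the selenium and vitamin E slope differences either as main effects or within levels of the other supplement, following the rule in the Results section. For main effects, use centred (+/-0.5) coding or drop the three-way term; with 0/1 dummies and that term present, time x selenium is the effect without vitamin E only.

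The cost is a slightly more complex model and a change of wording. The visits already scheduled supply the data.
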